### Follow-Up Procedures: 12-Month and 24-Month Visits

At 12 months of age (±7 days), the study participant returns to the Children's Hospital CTRC to complete their end of intervention visit. The visit includes the same procedures and sample collections as the baseline visit. The dietary intervention ends at 12 months. At the 12-month visit, caregivers are asked whether they want to consent to a 24-month follow-up visit. If so, caregivers sign another consent for the 24-month follow-up. When the participant turns 24 months, 1 year after the intervention ends, they come back to the Children's Hospital CTRC and repeat the procedures at baseline and 12 months, except for body composition and total energy expenditure assessment.

### Primary Outcomes

1) *Infant growth*

Pediatric nurses at the Children's Hospital Colorado CTRC (at baseline, 12 and 24 months) and study coordinators (at monthly home visits) obtain a series of infant anthropometric measurements. These measurements including weight (Seca^TM^ 337 infant scale), length (obtained in recumbent position using an infant stadiometer), and head circumference-for-age (Seca infant head circumference measuring tape). Growth Z scores are calculated using length and weight based on WHO/CDC standards (32).

2) *Body composition and total energy expenditure at 5 and 12 months of age*

At baseline and 12 months, a pre-dose urine sample is collected to document basal enrichment of ^2^H and ^18^O, then 0.1 g/kg body weight 99% enriched ^2^H_2_O and 0.3 g/kg 10% enriched H${}_{2}^{18}$O are orally administered. Caregivers are asked to collect one daily sample for 7 days post-dosing. Urine samples are analyzed for ^18^O and ^2^H enrichment by Off-Axis Integrated Cavity Output Spectroscopy (OA-ICOS, Los Gatos Research Inc., Mountain View CA) (33). Isotope dilution space will be calculated via the standard equation of pre-dose and zero-time intercept enrichment via back-extrapolation, which is validated in infants (34). Total body water will be calculated from dilution space × 1.04 to account for water exchange in non-aqueous tissues. Finally, total fat-free mass will be obtained from total body water ÷ age/sex-specific hydration factor (i.e., 79% for 6-month-old infants). CO_2_ production, obtained from the fractional turnover rates of ^2^H and ^18^O (35), is converted to total energy expenditure via Weir equation (36).

3) *Gut microbiota*

Caregivers will obtain a fresh stool sample each month of participation (5–12 months of age) and one at 24 months. 16S rRNA gene amplicon sequencing (37–39) will be performed on all samples to profile fecal bacterial communities. Following sequence QA/QC (37–39), 16S rRNA gene sequences are classified using the SINA/Silva classifier.

Shotgun metagenomic sequencing (40) will be performed on baseline and 12-month samples to determine the functional genomic capacity of fecal microbiota and broaden taxonomic profiles to include archaea, bacteriophage, DNA viruses, and microbial eukaryotes. Following sequence QA/QC, ***[1–4]*** sequences will be co-assembled with MEGAHIT ***[5]***, open reading frames predicted (Prodigal ***[6]***), and annotated using DIAMOND ***[7]*** to query the NCBI non-redundant database. Bacterial species and strains are inferred using MIDAS ***[8]***.

All sequences and associated metadata will be deposited in the NCBI sequence read archive, following the MIMARKS standard.

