#### Hypotheses

Primary: Growth trajectories (weight, length and body composition) and gut microbiota (diversity and composition) during early complementary feeding will differ by types of protein-rich foods consumed. Specifically, meat- and plant-based diets will have a lower weight-for-length Z score and adiposity, more age-appropriate and diverse gut microbiota than dairy and the reference groups. Secondary: A more mature, diverse microbiota will be positively associated with infant growth and that diet-induced infant growth trajectories will be mediated by the gut microbiota.

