##### Biospecimen Samples

At the baseline visit, pediatric nurses at the CTRC draw blood from all able participants via venipuncture (3–5 ml). Samples are centrifuged, and serum is stored at −80°C until analyzed. Individual aliquots will be used to measure ICF-1, ICFBP3, insulin, blood lipids (triglycerides, HDL, LDL and total cholesterol), alpha 1-acid glycoprotein (AGP), high sensitivity C-reactive protein (CRP), and quantitative amino acids. After the baseline visit at the Children's Hospital Colorado CTRC, urine samples (one pre-dose and seven post-dose) are collected by the caregiver to assess total energy expenditure and two-compartment body composition using the doubly labeled water technique (29). Urine samples are collected by placing cotton balls in the diaper and after soaked with urine, cotton balls will be placed in the barrel of a 20 ml sterile syringe and urine will be expressed into a sterile plastic tube. A stool sample is also collected from participants' homes for gut microbiota analysis. Stool samples are collected by placing a diaper liner in the infant's diaper, which allows urine to pass and stool to stay. Caregivers are advised to collect the soiled diaper liner and keep it in the home freezer before the study coordinator retrieves it. Lastly, a fasting breastmilk sample is collected from caregivers who are breastfeeding. Macronutrient and energy profiles of breastmilk are assessed via mid-infrared spectroscopy (Human Milk Analyzer, Miris, Uppsala, Sweden). Detailed instructions on how to collect urine, stool and breastmilk samples, and sample collection kits are provided to caregivers.

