### Dietary Intervention

Participants in the three intervention groups are asked to avoid protein-rich foods from other assigned groups (30) and consume protein only from their assigned group. All complementary foods, including infant cereal, low-protein fruits and vegetable purees, and designated protein-rich foods are provided to the three intervention groups. For formula-fed infants, the same brand cow-milk based infant formula is provided. The most recent NHANES report showed that the median protein intake of US infants 6–11 months (31) is 10% total energy or 2.5 g/kg/d. This quantity is used as the targeted total protein intake. Caregivers of infants in the reference/control group are given compensation to purchase complementary foods. Based on weight recorded at the visit and the reported formula/breastmilk intake, a recommended amount of meat- dairy- or plant-based food will be provided to caregivers to approximate a total protein intake of 2.5 g/kg/d. This estimation is updated every month. A sample diet plan is in Table 1, based on a formula-fed infant with a 60th percentile weight-for-age at 9 months.

**Table 1 T1:** Examples of diet plans for the three intervention groups^a^.

	**Food item**	**Protein**	**Calorie**
Total	Total calorie needs		~650 kcal/d
	Total protein (2.5 g/kg/d)	21 g/d	84 kcal/d
Formula (not restricted)	Formula 18 ounces	9 g/d	400 kcal/d
Dairy group^b^	1 Yogurt (Yobaby^®^)	4 g/d	80 kcal/d
	Cheese (shredded) (Horizon^®^)	6.5 g/d	80 kcal/d
	Others (e.g., 1 Beech Nut^®^ zucchini and banana blend; or one servicing of fortified rice cereal)	1 g/d	
Meat group^b, c^	1.5 jar of ham and gravy (Gerber^®^)	10 g/d	80 kcal/d
	Others (e.g., 1 Beech Nut^®^ zucchini and banana blend; or one servicing of fortified rice cereal)	1 g/d	
Plant group^d^	1.5 vegetable pouch (e.g., Ella's kitchen^®^ four bean feast)	5 g/d	90 kcal/d
	1.5 vegetable pouch (e.g., Earth's best^®^ spinach lentil)	5 g/d	50 kcal/d
	Others (e.g., 1 Beech Nut^®^ zucchini and banana blend; or one servicing of fortified rice cereal)	1 g/d	
Reference group	No restriction (observational group and will follow standard of care)		

a *These estimates are based on an exclusively formula-fed 9-month-old female with a 8.5 kg body weight which is ~60th percentile weight-for-age*.

b *Both Dairy and Meat groups are advised to avoid plant foods of relatively high protein contents (a list will be provided). Cheese will be shredded before providing to the infant*.

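### Total body water is obtained by multiplying the dilution space by 1.04, but the reason given requires division; followed as written, fat-free mass would be 8.2% too high and fat mass far too low

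*Protocol article*

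**What the plan says.** The second item under Primary Outcomes in the protocol article is headed "Body composition and total energy expenditure at 5 and 12 months of age". Two labels, deuterium and oxygen-18, are given by mouth. A dilution space is calculated from the pre-dose enrichment and the enrichment extrapolated back to time zero. The text then gives two conversions:

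- Dilution space to body water: "Total body water will be calculated from dilution space × 1.04 to account for water exchange in non-aqueous tissues".
- Body water to lean tissue: "total fat-free mass will be obtained from total body water ÷ age/sex-specific hydration factor", with 79% given as the factor at 6 months.

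The Biospecimen Samples section states that the purpose is to "assess total energy expenditure and two-compartment body composition using the doubly labeled water technique", so fat mass is body weight minus fat-free mass. The Hypotheses section relies on the result: "meat- and plant-based diets will have a lower weight-for-length Z score and adiposity". The conversion appears nowhere else in the article, and nothing reverses it.

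**The concern.** The first conversion gives both an operation and a reason, and they point in opposite directions. Some of the label leaves the water pool by exchanging with non-aqueous tissue. The enrichment left in body water is then lower, and the apparent space (dose divided by enrichment) is larger than the true volume of body water. Correcting for this means reducing the space. The written rule increases it, so the bias is compounded instead of removed.

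The error would pass into every fat-free mass, fat mass and percent-fat value at 5 and 12 months. Absolute body composition would be wrong as published, and comparison with outside values would mislead. Because fat mass is a remainder, its error depends on lean mass, so a difference in lean mass between diets, or lean growth between visits, would show up partly as a difference or change in fat.

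**Working it through.** **Inputs**

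- Factor 1.04, applied by multiplication, with its reason: Primary Outcomes, item 2.
- Hydration factor 0.79 (stated for 6 months): same item. It cancels from all relative errors.
- Fat mass = weight − fat-free mass: two-compartment model, Biospecimen Samples.
- Illustrative weight 8.5 kg, from the Table 1 footnote ("exclusively formula-fed 9-month-old female with a 8.5 kg body weight"). It cancels from all relative errors.
- True body-fat fraction *f*: not in the documents. Assumed, and varied from 15% to 35%.

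The article reports no body water, fat-free mass or fat-mass value, so there is no figure of its own to reproduce.

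**Step 1, direction.** Write D for the dilution space and TBW for true body water. The stated reason gives D = TBW + an exchangeable non-aqueous pool, so D > TBW. With the factor 1.04, D = 1.04 × TBW, hence TBW = D ÷ 1.04.

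**Step 2, the rule as written.** TBW(written) = 1.04 × D = 1.04 × 1.04 × TBW = 1.0816 × TBW.

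**Step 3, fat-free mass (FFM).** Both versions are divided by the same hydration factor, so FFM(written) ÷ FFM = 1.0816. FFM is 8.16% too high for every infant.

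**Step 4, fat mass (FM).** FM(written) − FM = −0.0816 × FFM. As a proportion of true fat mass, the error is −0.0816 × (1 − *f*) ÷ *f*.

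**Step 5, worked example at 8.5 kg and *f* = 25%.** FFM = 8.5 × 0.75 = 6.375 kg; TBW = 0.79 × 6.375 = 5.036 kg; D = 1.04 × 5.036 = 5.238 kg. Dividing by 1.04 recovers 5.036 kg. Multiplying gives 5.447 kg, which exceeds the space that already overstates body water. Then FFM(written) = 5.447 ÷ 0.79 = 6.895 kg, and FM(written) = 8.5 − 6.895 = 1.605 kg against a true 2.125 kg.

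| Assumed true fat | FFM true → written (kg) | FM true → written (kg) | FM error | Percent fat as written |
|---|---|---|---|---|
| 15% | 7.225 → 7.815 | 1.275 → 0.685 | −46.2% | 8.1% |
| 20% | 6.800 → 7.355 | 1.700 → 1.145 | −32.6% | 13.5% |
| 25% | 6.375 → 6.895 | 2.125 → 1.605 | −24.5% | 18.9% |
| 30% | 5.950 → 6.436 | 2.550 → 2.064 | −19.0% | 24.3% |
| 35% | 5.525 → 5.976 | 2.975 → 2.524 | −15.2% | 29.7% |

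**Step 6, comparisons between diets.** Writing Δ for a group difference, ΔFM(written) = ΔFM − 0.0816 × ΔFFM.

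- FFM differences are multiplied by 1.0816, a pure rescaling.
- At equal weight, ΔFFM = −ΔFM, so the fat-mass difference is also multiplied by 1.0816. For 25% against 28% fat at 8.5 kg, a true 0.255 kg becomes 0.276 kg.
- With equal true fat and an illustrative 0.5 kg difference in FFM, a spurious fat difference of 0.0816 × 0.5 = 0.041 kg appears, with the leaner-tissue group looking less fat.
- Within an infant, fat gain from 5 to 12 months is understated by 8.16% of the gain in FFM.

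**The case against.** The strongest reply is that the document shows a sentence, not a calculation. The article condenses a fuller protocol, cites a validated back-extrapolation method, and reports no derived values. The laboratory may well divide, in which case only the text is wrong. That is possible and cannot be ruled out here, so the numerical consequences are conditional on the text being followed. It does not rescue the sentence, since anyone programming from it would get wrong values. A printing or extraction fault is unlikely, because the division sign in the next sentence came through intact.

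The effect on randomised comparisons is also limited. The same constant applies to all four groups, so tests on fat-free mass are unaffected, and with no lean-mass difference the fat-mass contrast in kilograms is unchanged. This stands. The main damage is to absolute fat mass, percent fat and relative differences, with a usually modest distortion of fat contrasts where lean mass differs.

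Further, the Aim 1 model names length-for-age and weight-for-length Z scores, and the power calculation rests on growth Z scores, growth velocity and microbiota measures. None of these uses the formula. This narrows the reach of the error, but body composition is still listed as a primary outcome and adiposity is still in the primary hypothesis.

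Finally, the article does not say which isotope's space takes the factor. That bears on the right size of the divisor, not on the direction, and using a single isotope's space is not in itself a mistake. Energy expenditure would be affected only if this body water value enters the carbon dioxide calculation. The article mentions only turnover rates at that step, so no figure for energy expenditure is claimed.

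**Conclusion.** The formula is wrong as written: multiplication contradicts the reason stated in the same sentence, and division is required. If the rule is followed literally, fat-free mass is 8.16% too high for every infant. This rests only on 1.04 being the intended factor for the space used. The fat-mass error further depends on true body fat, which the documents do not give: a quarter too low near 25% fat, and between 15% and 33% too low as body fat ranges from 35% down to 20%. Whether any data have been affected depends on what the laboratory computes. Since the rule governs a listed primary outcome, it must be corrected.

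**What to change.** Replace the conversion with total body water = dilution space ÷ 1.04. State which isotope's dilution space is used, and give the divisor that belongs to it if it is not 1.04. Ask the laboratory to confirm the operator and divisor in its calculation sheet or program. If it already divides, only the text changes. If it multiplies, rederive body water, fat-free mass, fat mass and percent fat at both visits, and also energy expenditure if the same body water value feeds into it. The cost is one line in the protocol and analysis plan, a check of the calculation sheet and, at most, a rerun of one script. No new data or samples are needed.

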### Secondary Outcomes

1) *Dietary intake*

Three-day diet records are analyzed by the CTRC Nutrition Core using the NDSR software (Minneapolis, MN) by a trained dietitian. The Food and Nutrient Database in NDSR contains over 18,000 foods, including brand-name infant foods used in the proposed study. Outputs include total energy, carbohydrate (fiber, fructose, glucose, sucrose, starch, etc.), fat (cholesterol, different kinds of fatty acids), protein (meat, dairy, plant, breakdown of amino acids), vitamins and minerals. Macronutrient and energy profiles of breastmilk samples are assessed via mid-infrared spectroscopy (Human Milk Analyzer, Miris, Uppsala, Sweden).

2) *Blood biomarkers*

IGF-1, IGFBP3, insulin, blood lipids, alpha 1-acid glycoprotein (AGP), high sensitivity C reactive protein (hsCRP) and quantitative amino acids will be measured at the University of Colorado Anschutz Medical Campus CTRC Core lab (30).

### Power Calculation and Sample Size Justification

We hypothesize that both the gut microbiota and infant growth trajectories are dependent on types of protein-rich foods consumed. We will recruit up to 75 infants/arm and use a conservative 20% attrition which results in 60/group (total completers *n* = 240). Sample size and power justification are from the longitudinal models with feeding group as the predictor and either gut microbiota (i.e., diversity and *Ruminococcus* abundance) and growth (i.e., linear growth parameter LAZ, overweight parameter WLZ and growth velocity using the WHO 0–24 months standards) as the outcomes. We completed power simulations (1,000 replicates) using a linear mixed-effects model (LME) with random effects by subject. For the simulations, we used parameter estimates (e.g., fixed and random effects) from our randomized pilot study on the gut microbiota and infant growth trajectories after receiving meat- or dairy-based complementary diet (30). We simulated a variety of scenarios assuming that Plant had microbiota and growth outcomes that were either worse than Dairy, between Dairy and Meat, or the same as Meat. *To be conservative, we estimated power after increasing the within-group variability by 50%*. The power is above 80% in all simulated scenarios (80–90%) where the effect size was simulated to be at least 50% of that observed in our pilot study (30). The power of most simulation scenarios was below 80% when the effect size was 25% of that observed in the pilot study (30).

### Statistical Approach

Aim 1: Using ANOVA for continuous variables and chi-squared test for categorical variables, we will assess whether matching and randomness held by testing whether potential confounders (e.g., feeding mode, maternal height, maternal BMI, education, sex, race/ethnicity, and smoking during pregnancy) differ between groups. Variables with a *p* < 0.05 and those that have a strong association with the outcome of interest are included in future models. To model the relationship between diet, time, and diet by time interaction and LAZ and WLZ, we use LME model with random effects by subject. This structure explicitly models multiple time points per infant and can adjust for changes of cofounders during the intervention (e.g., a participant changed from breastfeeding to formula feeding at 9 months). Given a significant diet by time interaction, we will test pairwise differences in growth trajectories using Tukey's multiple comparisons.

Aim 2: We model the effects of diet on the gut microbiota at the end of the intervention and longitudinally, incorporating likely covariates and potential cofounders. 16S amplicon sequencing and metagenomic sequencing will each generate tables of annotated sequence counts. Both datasets will be used to model the diet's impact on microbiota taxonomic composition and functional capacity (i.e., genes and pathways identified through shotgun metagenomics) over the course of the intervention. To evaluate differences in overall taxonomic/functional community composition (i.e., beta-diversity), we use the Microbiota Regression based Kernel Association Test (MiRKAT). MiRKAT models the microbiota using phylogenetic kernels to account for differences in microbial profiles (16S or metagenomics count data) (41). As different measures of dissimilarity are optimal under different conditions, optimal-MiRKAT allows multiple dissimilarity metrics to be tested simultaneously. To model microbial taxonomic and functional profiles over time, we use two methods recently proposed (42). First, we use a bi-exponential distribution to summarize microbiota diversity curves over time. To make inferences, we will incorporate the distribution into a hierarchical model with a random intercept to account for multiple measurements for each person. This approach will model changes in individual taxa, both the rare and common, over time. Additionally, we will evaluate longitudinal changes in common alpha-diversity metrics (e.g., richness, evenness, Shannon diversity, and effective species [e.g., Hill's number (42)]). Finally, we use the control group to build a gut microbiota maturation model via a random forest approach as previously described (24) and compare the intervention groups to this model.

Aim 3: We use LME on growth Z scores and the microbiota over time with random effects by subject, and include group as a covariate. We also complete secondary analyses stratified by group to identify relationships between Z scores and microbiota that differ by group. We will use microbiota diversity measures and relative abundances of individual taxa and genes/pathways to model diversity and composition of the microbiota. We also include necessary confounders, e.g., change from breastfeeding to formula. To evaluate whether taxonomic and/or functional features of the microbiota mediate the relationship between diet and growth, we use a method and R package called MedTest (43). As in classic mediation analysis, MedTest evaluates three models (44). In reference to Figure 2, the first model estimates the direct path between protein-rich foods and the gut microbiota and implements as part of Aim 1 using MiRKAT. The second model estimates the path between protein-rich foods and infant growth and will be implemented using a standard linear model in R. The third model estimates the path between protein-rich foods and growth controlling for the path between gut microbiota and growth and will be implemented using MiRKAT. Using these three models, MedTest tests for significances of the mediation effect of the gut microbiota. Since it is unknown which microbiota features may mediate the relationship, MedTest implements multiple microbiota distances: unweighted (45), weighted (46), and generalized UniFrac (47) as well as Jaccard and Bray-Curtis distances. To ensure a well-controlled type-I error rate, MedTest uses a modified permutation procedure to arrive at an omnibus test over all distances.

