#### Randomization

Upon enrollment, participants are randomized into one of four groups, differentiated by source of protein-rich foods they consume (meat, dairy, plant or control group). A stratified random sampling design is used where the strata are defined by mode of feeding (breastfed or formula-fed), sex (male or female) and mode of delivery (cesarean or vaginal delivery). The four feeding groups are randomized within each strata in groups of four so each diet (Meat, Dairy, Plant, Reference) occurs exactly once per four enrollments. Given our rolling recruitment strategy over 4 years, this ensures that the initial randomization of group within each strata is close to balanced and that there is little to no relationship with the order of recruitment. A stratified randomization design controls for possible confounding variables and results in an increase in power.

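### Covariates are chosen by baseline significance tests and an undefined outcome-association rule, so the randomisation strata are not guaranteed to enter the models and the power gain claimed for stratifying is not secured

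*Protocol article*

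**What the plan says.** **Randomization section.** Infants are stratified by feeding mode, sex and mode of delivery, which gives 2 × 2 × 2 = 8 strata. They are "randomized within each strata in groups of four so each diet (Meat, Dairy, Plant, Reference) occurs exactly once per four enrollments". The section adds: "A stratified randomization design controls for possible confounding variables and results in an increase in power".

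**Statistical Approach, Aim 1.** Using ANOVA and chi-squared tests, "we will assess whether matching and randomness held by testing whether potential confounders" differ between groups. The examples given are feeding mode, maternal height, maternal BMI, education, sex, race/ethnicity and smoking in pregnancy. Delivery mode is not among the examples. Variables with p < 0.05 and "those that have a strong association with the outcome of interest are included in future models". No threshold is given for a strong association.

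The growth model itself is described as follows: "To model the relationship between diet, time, and diet by time interaction and LAZ and WLZ, we use LME model with random effects by subject". No stratification term and no baseline value are named as fixed parts of it. The gate to the pairwise tests is the interaction: "Given a significant diet by time interaction, we will test pairwise differences in growth trajectories using Tukey's multiple comparisons".

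**The concern.** The covariate rule is written into the protocol, so this is not a detail left open for the analysis plan. It has three weaknesses.

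- **The test answers no useful question.** If allocation was random, every baseline difference arose by chance. A p-value cannot show whether randomisation worked, and it says nothing about whether a variable predicts growth.
- **The test is empty for the stratification factors.** Feeding mode and sex are screened although the design forces them to balance. The factors most likely to have been chosen for their prognostic value are the ones this route will not pick.
- **The set depends on the data.** The second route is judged on the trial's own outcomes, without a threshold, so the adjustment set can differ from outcome to outcome.

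At stake is precision in comparisons of level between arms, and the credibility of models whose covariates are settled after the data have been seen. Such comparisons are planned: microbiota at the end of the intervention (Aim 2), the linear model of diet on growth (Aim 3), and body composition, a primary outcome measured only at 5 and 12 months.

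**Working it through.** **The plan's own figures.** Attrition reproduces: 75 × 0.80 = 60 per arm, and 4 × 60 = 240. The simulated power of 80–90% cannot be reproduced, because the pilot effect, the variances and alpha are not in the article. All power figures below are therefore illustrations. They use two-sided alpha 0.05, 60 per arm and an assumed share of variance.

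**1. Chance selection by p < 0.05.** Five of the named variables are not stratified: maternal height, maternal BMI, education, race/ethnicity and smoking. If the tests are independent, 1 − 0.95^5 = 0.226, or about 23% for at least one.

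**2. Can a stratification factor be selected by p < 0.05?** Simulation of 4,000 trials: 300 infants, 8 strata, blocks of four, assumed prevalences of 50%, 50% and 30%, and a 3-df chi-squared test per factor.

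| Allocation | p < 0.05, all 300 | p < 0.05, after 20% random dropout |
|---|---|---|
| Stratified blocks | 0 of 4,000 for each factor | 0 of 4,000 for each factor |
| Unstratified | about 5% | 5–6% |

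**3. Cost of omitting strata in a level comparison.** Start from 80% power with strata fitted: z(0.975) + z(0.80) = 1.960 + 0.842 = 2.802. If strata explain a share R² of between-infant variance and are left out, the SD used grows by 1/√(1 − R²):

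power = Φ(2.802 × √(1 − R²) − 1.960)

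- R² = 5%: Φ(2.731 − 1.960) = 78.0%
- R² = 10%: Φ(2.658 − 1.960) = 75.7%
- R² = 20%: Φ(2.506 − 1.960) = 70.7%

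This formula is slightly pessimistic here. With stratified allocation the estimate keeps its smaller true variance and only the reported standard error is too large. Then power = Φ(2.802 − 1.960/√(1 − R²)), which gives 78.5%, 76.9% and 72.9%. The same mismatch makes the test conservative: for a pairwise comparison the true alpha is 2Φ(−1.960/√(1 − R²)) = 4.4%, 3.9% and 2.8%.

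**4. Does this reach the diet-by-time test?** Simulated mixed model: 240 infants, 8 visits, random intercept and slope, assumed variance components.

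| Strata effect (assumed) | Quantity | SE, no strata | SE, strata main effects | SE, plus strata × time |
|---|---|---|---|---|
| Level only, R² 10% | Slope contrast | 0.0943 | 0.0943 | 0.0943 |
| Level only, R² 10% | 12-month level | 0.1818 | 0.1743 | 0.1743 |
| Level only, R² 20% | 12-month level | 0.1819 | 0.1666 | 0.1666 |
| Level R² 20%, slope 10% | Slope contrast | 0.0943 | 0.0943 | 0.0917 |
| Level R² 20%, slope 20% | Slope contrast | 0.0943 | 0.0943 | 0.0888 |

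Main effects help level comparisons. The slope test gains only if strata also predict slope and strata × time terms are fitted.

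**5. Use of the 5-month value.** For a 12-month comparison with 80% power when baseline is ignored, at an assumed baseline correlation r:

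- r = 0.5: change score 80.0%, ANCOVA 89.9%
- r = 0.7: change score 95.1%, ANCOVA 97.5%

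The variance ratio of ANCOVA to change score is (1 − r²)/(2(1 − r)) = (1 + r)/2, so 0.75 at r = 0.5 and 0.85 at r = 0.7.

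**The case against.** The strongest reply is that the article is condensed and that the full covariate list, the strata terms and the handling of baseline belong in the analysis plan. This stands for what is merely unstated. It does not cover the selection rule, which is stated.

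Several stronger readings are tempting, and the document does not support them:

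- **That the strata drop out of the model.** If the two routes are alternatives, a perfectly balanced stratum that is strongly prognostic still enters. Only if both conditions are required would the strata almost surely be excluded. The wording does not settle which is meant.
- **That delivery mode is left out.** The candidate list is introduced as examples, so nothing follows from its absence. Changes in feeding mode during the intervention are explicitly foreseen as an adjustment.
- **That the claimed power gain is lost, or that 80–90% is wrong.** The Randomization section puts no size on the gain. The power section names feeding group as the predictor and takes no stated credit for strata.
- **That the main growth test suffers.** Its gate is diet by time, which does not change if strata influence level only.
- **That baseline is ignored.** The article says "This structure explicitly models multiple time points per infant", so the 5-month value may already be the first response. In that case part of the gain in step 5 is already recovered.
- **That type I error is inflated by omitting strata.** The error runs the other way: the test is conservative.

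The 23% also rests on independence and on an open-ended list, and no resulting bias has been shown.

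**Conclusion.** The point holds in limited form. The protocol fixes a poor rule: it tests randomised groups for baseline differences to judge randomisation, and selects covariates by p < 0.05 or by an undefined association with the outcome. The first route essentially never admits the stratification factors and admits others by chance. The second depends on an unstated judgement made on outcome data. The strata are therefore not guaranteed to be fitted, and the benefit claimed for stratifying is not secured.

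The size depends on unknown prognostic strength. For level comparisons starting at 80% power it is a loss of about 2 to 9 points at strata R² of 5–20%, or about 1.5 to 7 points once the stratified allocation is allowed for. For the diet-by-time slope test it is nil if strata affect level only. This is an almost free improvement; it does not invalidate the planned analysis.

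**What to change.** 1. Delete the p < 0.05 screen and the strong-association rule. Present baseline characteristics by group descriptively, without tests.
2. In every diet model, always include baseline feeding mode, sex and mode of delivery. Add strata × time terms where the strata are expected to affect slope.
3. Name a short list of further prognostic covariates before outcome data are seen, and use the same list for all outcomes of one type.
4. State how the 5-month value is used: either as a response with a common baseline mean across arms in the mixed model, or as an ANCOVA covariate for 12-month outcomes such as body composition.

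The cost is a change of wording and a few degrees of freedom. No extra infants, visits or measurements are needed.
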